4.32 Compartmental Evaluations

4.321 Whole blood willbe collected for storage of plasma and PBMC samples (see Appendix II). The following evaluations will be performed unless totalblood volumes exceed safe limits (the American Red Cross has a limit of 450 mL of blood over 56 days for healthy volunteers):

 Plasma for HIV-1 genotypic resistance studies.

 PBMC storage for HIV-1 proviral DNA studies.

NOTE: If the subject is enrolled in other studies and blood volumes do not permit obtaining an additional blood sample for A5077, the A5077 protocol team will request access to plasma and PBMC samples from the coenrolled study(ies) (see Appendix II).

4.322 Saliva: Samples of saliva should be obtained, processed, stored, and shippedas outlined in Appendix III. The following evaluations will be performed:

 HIV-1 RNA quantitation.

 HIV-1 genotypic resistance studies.

 HIV-1 proviral DNA studies.

4.323 Genital Secretions and/or Lymphoid Tissues: Subjects have the option to contribute either genital secretions or lymphoid tissues, or both. Samples should be obtained, processed, stored, and shipped as outlined in Appendices IV and V. The following evaluations will be performed:

 HIV-1 RNA quantitation.

 HIV-1 genotypic resistance studies.

 HIV-1 proviral DNA studies.

## On Study Evaluations

Noncompartmental evaluations are required at week 8 and every 8 weeks thereafter until week 96, within 30 days of confirmed virologic failure (section 4.5), and at the time of premature study discontinuation (section 4.6). Compartmental evaluations are required at weeks 16, 48, 96, within 30 days of confirmed virologic failure (section 4.5), and at the time ofpremature study discontinuation (section 4.6).

4.41 Noncompartmental Evaluations:

4.411 Clinical assessment to include updated signs/symptoms and new HIV-related diagnoses.

NOTE: If any signs or symptoms of a genitourinary tract infection are noted, the subject should be evaluated and, if indicated, treated. Sampling of genital secretions should be delayed until the infection is resolved.

4.412 Medication update to include changes in anti-HIV medications, immune-based therapies, and HIV vaccines.

4.413 Hematology: CBC with differential.

4.414 CD4 and CD8 cell counts (absolute and percentage).

4.415 Plasma HIV-1 RNA (using the UltraSensitive Roche assay; see Appendix II).

4.42 Compartmental Evaluations

4.421 Whole blood willbe collected for storage of plasma and PBMC samples (see Appendix II). The following evaluations will be performed unless total blood volumes exceed safe limits (the American Red Cross has a limit of 450 mL of blood over 56 days for healthy volunteers):

 Plasma for HIV-1 genotypic resistance studies.

 PBMC storage for HIV-1 proviral DNA studies.

NOTE: If the subject is enrolled in other studies andblood volumes do not permit obtaining an additional blood sample for A5077, the A5077 protocol team will request access to plasma and PBMC samples from the coenrolled study(ies) (see Appendix II).

4.422 Saliva: Samples of saliva should be obtained, processed, stored, and shipped as outlined in Appendix III. The following evaluations will be performed:

 HIV-1 RNA quantitation.

 HIV-1 genotypic resistance studies.

 HIV-1 proviral DNA studies.

4.423 Genital Secretions and/or Lymphoid Tissues: Subjects have the option to contribute either genital secretions or lymphoid tissues, or both. Samples should be obtained, processed, stored, and shipped as outlined in Appendices IV and V. The following evaluations will be performed:

 HIV-1 RNA quantitation.

 HIV-1 genotypic resistance studies.

 HIV-1 proviral DNA studies.

## Virologic Failure Evaluations

4.51 Criterion for Virologic Failure

Subjects with suspected virologic failure (defined as HIV-1 RNA level > 200 copies/mL > 16 weeks after initiating or changing potent antiretroviral therapy) will be required to return to the clinic to have a confirmatory blood plasma HIV-1 RNA performed within 30 days.

NOTE: Since any vaccination or acute illness may cause an increase in viral load, specimens should be collected at least 14 days after vaccination or acute illness whenever possible.

4.52 Virologic Failure Evaluations

Virologic failure evaluations must be performed within 30 days of confirmedvirologic failure (i.e., within 30 days from the date of the confirmatory HIV-1 RNA). The evaluations required at the time of virologic failure are the same as those required at week 96 (see section 4.4).

After subjects have the virologic failure evaluations performed, they should remain on study and resume their regularly scheduled study visits until week 96. Subjects who change their antiretroviral drug regimens during their participation in A5077 should also continue on study and have the required protocol evaluations performed until their week 96 visit.

NOTE: Subjects should only have the virologic failure evaluations performed the first time virologic failure is confirmed during their participation in A5077. Subjects who experience confirmed virologic failure subsequently while still participating in A5077 should NOT have the virologic failure evaluations performed again.

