A5077 is designed to analyze relationships between viral load in blood and nonblood compartments and time to virologic failure in subjects initiating or changing potent antiretroviral therapy. The virologic analyses in blood and nonblood compartments that are planned as part of this protocol might help to better segregate subjects with suppressed plasma HIV-1 RNA levels and identify those subjects who will subsequentlydevelop virologic failure. Of particular interest are cross-sectional and longitudinal analyses of blood and nonblood compartmental samples obtained from subjects at the following time points: 1) at study entry (baseline); 2) at the time of virologic suppression in plasma (< 200 HIV-1 RNA copies/mL); 3) at the time of virologic failure (HIV-1 RNA levels > 200 copies/mL); and 4) during follow-up. Characterization of the viral burden (HIV-1 RNA, proviral DNA) and other characteristics of the virus (genotypic resistance patterns, viral evolution, synctium-inducing/nonsynctium-inducing (SI/NSI), fitness, etc.) in blood and in specimens from nonblood compartments collected at these time points will contribute to the understanding of the virologic factors influencing the long-term effects of potentantiretroviral therapy.

A5077 includes sampling of lymphoid tissues from study participants because lymphoid organs constitute a major HIV-1 reservoir and are primary sites for HIV-1 replication (7,8). By using in situ hybridization and other quantitative methodologies, it has been possible to characterize and quantitate the different pools of HIV-1 in the lymphoid organs of infected individuals (7-9). Quantitative virologic studies in lymphoid tissue specimens obtained from antiretroviral-naïve individuals have shown that potent antiretroviral therapy that reduces plasma HIV-1 RNA to undetectable levels is also associated with significant reductions in the amount of HIV-1 in lymphoid tissues (10,11). These reductions in tissue viral burden are the consequence of a decline in the follicular dendritic cell (FDC)-associated virus together with a reduction of HIV-1 mRNA expression and proviral HIV-1 DNA in tissue CD4+ mononuclear cells. Despite these reductions, HIV-1 is still present in lymphoid tissues of individuals with suppressed plasma HIV-1 RNA levels (10).

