Because of the importance of the genital tract in the transmission of HIV-1, A5077 includes sampling of genital secretions from study participants for virologic studies. Relatively few studies have been conducted investigating HIV-1 expression, viral evolution, and the effects of potentantiretroviral therapy in this compartment. Data from several cross-sectional studies suggest that 60%-75% of men shed HIV-1 RNA in the seminal plasma and that 65%-80% have detectable HIV-1 DNA in seminal cell pellets (15-18). Similar studies in women demonstrate considerably more variation, with 30%-88% of women having detectable HIV-1 RNA in the genital tract, and 40%-70% having detectable HIV-1 DNA in this compartment (19-23). Most of this variation is probably attributable to differences in the method used for sample collection (vaginal swab versus cervical swab versus cervicovaginal lavage), as well as to differences in the assays used to determine viral load (commercial versus in-house assay) (24,25). However, additional variation in viral HIV-1RNA levels may arise from the hormonal effects of menses on viral shedding from the endocervical canal (26). Despite these differences, the overall conclusions from these studies have been quite similar. HIV-1 levels in the genital tract are generally lower than those observed in the blood at the same time, but still correlate significantly with HIV-1 RNA levels in plasma. However, there are a few individuals who have an HIV-1 viral load level in the genital tract that is considerably greater than their viral load level in plasma (22,27).

Longitudinal studies involving subjects initiating potentantiretroviral therapy have demonstrated that the decrease of the viral load in the genital tract parallels that in the blood (17,22,28,29). In a small study of subjects with plasma HIV-1 RNA levels < 400 copies/mL for at least 2 years, HIV-1 RNA was present in 1/21 seminal plasma samples and 2/2 cervical specimens (30). In a larger study of 114 men with similar plasma HIV-1 RNA levels, only 2 (2%) had detectable HIV-1 RNA in seminal plasma, and 16% had detectable HIV-1 DNA in seminal cells (31). Using more sensitive techniques, proviral HIV-1 DNA was detected in the seminal cells of 4 of 7 men with long-term suppression of HIV-1 in blood plasma, and HIV-1 was isolated from the seminal cells of two of the men (32). In contrast

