## EntryEvaluations

Entry specimens must be obtained prior to changing or initiating potent antiretroviral therapy. Study entry evaluations should be performed within 30 days of the screening evaluations. Preentry and entry evaluations should be separated by at least 24 hours.

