2.0 SPECIMEN COLLECTION, PROCESSING, AND STORAGE

NOTE: SPECIMENS MUST BE DELIVERED TO THE LABORATORY AND PROCESSED WITHIN 48HOURS OF COLLECTION

A. Specimen Collection

ONE 10.0 mL purple-top EDTA tube (Becton Dickinson re-order number #6457) will be drawn from all subjects at preentry,entry, week 8 and every 8 weeks thereafter until week 96, within 30 days of confirmed virologic failure, and at the premature study discontinuationvisit.

B. Specimen Processing

1. Clarified plasma

To minimize RNA degradation, all plasma samples must be processed and stored at -70°C within 48 hours of collection. Although the required processing time has been increased from 4-6 hours to 48 hours, sites are encouraged to continue to process HIV-1 RNA samples as soon as possible. Specifically, the EDTA tube should be centrifuged at low speed (400 x *g*) for 10 minutes at room temperature as soon as possible after collection.

Plasma should be carefully removed from each tube, placed in a sterile polypropylene conical centrifuge tube and centrifuged again (at 800 x *g*) for 10 minutes to completely remove platelets and cell debris. Store as many 1.2 mL aliquots of plasma as possible at –70°C.

2. PBMCs

After plasma has been removed as indicated above, PBMCs will be obtained and stored according to procedures outlined in the AACTG Virology Manual for HIV Laboratories (January 1997 version).

Store TWO TO FOUR aliquots of 2 x 106 cells as NON-VIABLE DRY cell pellets at - 70°C.

C. Real Time Plasma HIV-1 RNA

NOTE: Participating sites should try to avoid virologic sampling for confirmatory testing during an intercurrent illness, within 14 days after a subject receives an immunization or within 14 days of a dose interruption, as this may result in a transient elevation of plasma HIV-1 RNA levels.

Within ten (10) business days following the receipt of a plasma sample(s) by the ACTG-specified laboratory for the performance of real time plasma HIV-1 RNA assays, the designated laboratory will FAX the results to the clinic. Upon receipt, the clinic is to key the results into the central ACTG database.

If the result provides the first suggestion of a virologic failure, the subject should be recalled to the clinic to have a confirmatory virologic (plasma) specimen obtained. Every attempt should be made to have the confirmatory sample drawn as soon as possible, but no later than 30 days after the date of the first sample.

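### Section 4.52 does not require failure-visit specimens to precede a regimen change, so a nonblood sample re-suppressed by new drugs can be counted as blood-first evidence for objective 2.21

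*Protocol*

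**What the plan says.** Section 4.52 asks for the week 96 evaluations at confirmed failure: stored plasma and PBMC, saliva, and genital secretions or lymphoid tissue or both. Its one timing rule is "i.e., within 30 days from the date of the confirmatory HIV-1 RNA". These evaluations are done only at the first confirmed failure.

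The same section foresees treatment changes: "Subjects who change their antiretroviral drug regimens during their participation in A5077 should also continue on study". Section 6.0 says that the study supplies no treatment.

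At entry the order is fixed. Section 4.3 states: "Entry specimens must be obtained prior to changing or initiating potent antiretroviral therapy".

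Appendix II, section 2.0 C, makes plasma HIV-1 RNA a real-time test. The confirmatory draw is due "no later than 30 days after the date of the first sample". The turnaround is "Within ten (10) business days following the receipt of a plasma sample(s) by the ACTG-specified laboratory", when "the designated laboratory will FAX the results to the clinic".

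Section 1.1 names the failure sample as one of four time points of particular interest: "3) at the time of virologic failure (HIV-1 RNA levels > 200 copies/mL". Section 7.54 compares the timing of blood and nonblood events with a sign test. It uses only subjects whose order can be determined, allowing for interval censoring.

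**The concern.** The failure visit is the one nonblood collection tied to plasma failure; the other on-study collections are at weeks 16, 48 and 96 or at premature discontinuation. It is meant to show the compartments while the regimen is failing. The clinic may know of the failure before the specimens are taken and may change treatment first. The specimens then show the compartments under new drugs and still comply with the protocol.

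The Protocol gives a reason to expect an effect. Section 1.1 reports that, in subjects starting potent therapy, "the decrease of the viral load in the genital tract parallels that in the blood". At stake are secondary objectives 2.21 (where suppression is lost first) and 2.22 (where new mutations appear first), and the description of virus at failure. A specimen missed before a change cannot be recovered later.

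**Working it through.** The plan gives no figure that depends on this order, so there is none to reproduce. The check compares the timing rules, adds up the windows and follows one subject through Section 7.54.

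**1. Is the order stated elsewhere?** Sections 1.2, 4.4 and 7.1, the Schedule of Events and Appendices II to V repeat the failure visit or its 30-day window without it. Section 4.51 and Appendix II advise on sampling around vaccination, acute illness and, in Appendix II, dose interruption. Neither mentions a regimen change.

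**2. How long could a new regimen have acted?** Inputs from the Protocol: 30 days to the confirmatory draw, 30 more to the failure specimens, and 10 business days from laboratory receipt to result, about 14 calendar days. Assumption: 0 to 7 days to reach the laboratory (Appendix II allows shipment Monday to Wednesday only).

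- First value above 200 copies/mL to last permitted specimen: 30 + 30 = 60 days.
- Change on the confirmatory result: 30 − 14 − shipping = 16, 13 or 9 days for 0, 3 or 7 days of shipping.
- Change on the day of the confirmatory draw: up to 30 days.
- Change on the first, unconfirmed result: 60 − 14 − shipping = 46 to 39 days.

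The second and fourth lines take the laboratory's full allowance, a change on the day of the result and the last permitted sampling day. A faster result would lengthen the exposure; a later change or earlier sampling would shorten it.

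**3. What does the sign test do with such a specimen (2.21)?** Take a subject with nonblood suppressed at week 16, plasma suppressed at week 24 and above 200 at week 32, confirmatory draw at week 36, and failure specimens at week 40 (28 days later, within the limit).

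| Failure specimen | Blood event | Nonblood event | Result under 7.54 |
|---|---|---|---|
| Nonblood detectable | weeks 24–32 | weeks 16–40 | intervals overlap, subject excluded |
| Nonblood suppressed | weeks 24–32 | after week 40 | blood first, subject counts |

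The failure specimen is always later than the plasma event that triggers it. A detectable result can therefore never show nonblood first, and a suppressed result can only show blood first. If the compartment had lost suppression and a new regimen restored it before sampling, a subject who should be excluded becomes a blood-first vote. The specimen makes no difference where a scheduled nonblood sample has already settled the order.

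**4. Does the same follow for resistance (2.22)?** No. Plasma and PBMC for genotyping are collected at the same visit, under the same window. A change before sampling can alter blood and nonblood genotypes alike.

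**5. How far might a nonblood level fall?** The documents give no rate. Assume a start of 1,000 copies/mL and a fall of 0.5 to 1.5 log10: 1,000 × 10^−0.5 = 316 and 1,000 × 10^−1.5 = 32 copies/mL. Reaching 50 needs log10(1,000/50) = 1.30, so (1.30 − 0.5)/1.0 = 80% of that range stays above 50. With assumed half-lives of 2, 5, 10 and 20 days instead, 1,000 × 0.5^(16/half-life) gives about 4, 109, 330 and 574 copies/mL after 16 days. The direction is the same throughout; the size depends on the assumption.

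**The case against.** **Treatment change is conditional.** Section 4.52 speaks of subjects who change, not of an expected change. A reader might infer that most failure specimens would be taken after a switch; the documents give no frequency. This stands.

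**A reader might infer that resistance, too, is biased towards blood first.** The shared window in step 4 does not support that. Section 1.1 also reports that genital HIV-1 DNA does not seem to respond to therapy, and the appendices turn to cell DNA for saliva and genital genotyping when RNA is below 1,000 copies/mL. What remains is lost information and poor comparability between subjects sampled before and after a change.

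**A reader might infer that post-change samples would usually be undetectable.** Step 5 does not support that for most of the assumed 0.5 to 1.5 log10 range. The statement in Section 1.1 concerns the genital tract in subjects starting therapy and gives no time scale.

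**Records allow flagging.** Section 4.0 requires all antiretrovirals to be recorded, and a medication update and plasma HIV-1 RNA belong to the failure visit. An analysis plan not seen here could exclude or flag post-change specimens. This weakens the analysis part of the point but not the collection part, because flagging cannot restore the state before the change.

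**The 30 days have practical reasons.** Genital collection needs 48 hours of abstinence, and tonsillar biopsy or node aspiration two weeks without aspirin or NSAIDs. This is a fair argument for keeping the window, and the fix keeps it.

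**Conclusion.** The point holds as a gap in specimen timing with limited reach. A compliant failure specimen can be taken after a regimen change: about 9 to 16 days after it if the change follows a confirmatory result that takes the full turnaround, and up to 30 to 46 days if the change comes earlier. For objective 2.21 the resulting error favours blood first. Its size cannot be derived, because it depends on how many subjects change before sampling, the nonblood level at failure, the rate of fall and the threshold used. For objective 2.22 only a loss of information and comparability is shown.

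No primary analysis is affected: both failure endpoints in Section 7.2 use plasma HIV-1 RNA, and virus detection uses week 48 specimens from persistently suppressed subjects. The reading of the sign test rests on Section 7.54 as written; a separate analysis plan might refine it.

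**What to change.** In Section 4.52 and the Schedule of Events footnotes on compartmental samples, state that failure specimens, including stored plasma and PBMC, should be collected before any change of regimen whenever this does not delay that change, and otherwise as soon as possible within the existing 30 days. Record the date of each specimen and of any regimen change.

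In Section 7.54, or in the analysis plan, do not count a specimen taken after a regimen change as failure-time evidence that a compartment was still suppressed or free of new mutations. Alternatively, report the sign test with and without such specimens. Reporting both has a merit: dropping them also removes subjects in whom blood truly failed first.

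The cost is a few sentences, a date check on the case report form, slightly tighter scheduling and some specimens lost to the secondary analyses. No extra collection is needed, in particular no genital sampling at the confirmatory visit in subjects whose failure may not be confirmed. No treatment decision is changed.

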## Premature Study Discontinuation

Subjects who discontinue the study before week 96 must have the evaluations required at week 96 performed within 30 days of premature discontinuation. If a study visit in which compartmental evaluations was performed within 30 days prior to premature study discontinuation, these evaluations do not need to be repeated.Please refer to section 6.1 for the criteria for study discontinuation.

# DATA COLLECTION AND MONITORING AND ADVERSE EXPERIENCE REPORTING

## Records to Be Kept

Case report forms (CRFs) will be provided for each subject. Subjects must not be identified by name on any study documents. Subjects will be identified by the Patient Identification Number (PID) and Study Identification Number (SID) provided by the ACTG Data Management Center upon (randomization/ registration).

All data on the CRF must be legibly recorded in black ink or typed. A correction should be made by striking through the incorrect entry with a single line and entering the correct information adjacent to it. The correction must be initialed and dated by the investigator or a designated qualified individual. Any requested information that is not obtained as specified in the protocol should have an explanation noted on the CRF and in the source document as to why the required information was not obtained.

## Role of Data Management

5.21 Instructions concerning the recording of study data on CRFs or the entry of data in the computerized database will be provided by the ACTG Data Management Center. Each ACTU is responsible for keying the data in a timely fashion.

5.22 It is the responsibility of the ACTG Data Management Center to assure the quality of computerized data for each ACTG study. This role extends from protocol development to generation of the final study databases.

## Regional Monitoring

5.31 Site monitors under contract to the National Institute of Allergy and Infectious Diseases (NIAID) will visit participating clinical sites to review the research records for accuracy, completeness, and legibility. The monitors also will inspect sites' regulatory files to ensure that regulatory requirements are being followed.

5.32 Site visits will be made at main units and the larger subunits at standard intervals and more frequently as directed by NIAID.

5.33 The investigator will make study documents (e.g., consent forms, CRFs) and pertinent hospital or clinic records readily available for inspection by the site monitors for confirmation of the study data.

